## 5. TREATMENT OF SUBJECTS

All included patients are already scheduled for surgery. Participation will not influence the waiting time. If patients decide to participate, additional burden is dependent on randomization. All patients will be asked to take quality of life and side effects questionnaires before surgery and at 3 and 12 months after surgery. The questionnaires take approximately 20 minutes per time point.

Patients who are randomized to the conventional arm will be operated according to current clinical practice. These patients will undergo one additional CT scan with contrast (10 minutes) in the two weeks before surgery on which the target lymph nodes will be indicated. In the control arm, no 3D anatomical models will be generated.

Patients in the experimental arm will be operated with assistance of the in-house developed navigation system. One extra contrast enhanced CT scan before surgery will be acquired in the two weeks before surgery (10 minutes). During surgery, three Patient Trackers are attached to the skin of the patient using medical tape, not obstructing the surgical field. An additional intra-operative CT scan is acquired ( $\pm 10$  minutes) for calibration, which will be an addition to the total time of

anaesthesia. The surgeon will have a sterile tracked navigation pointer which can be used to correlate the actual anatomy of the patient with a 3D model derived from pre-operative imaging (Fig. 2). With this setup, the surgeon is provided with a view beyond surgical plane. After opening the abdomen, some anatomical landmarks will be used to verify the navigation accuracy, which will take a maximum of 5 minutes. Subsequently, the navigation system can be used to localize the targeted lymph nodes.

We will try to plan the additional pre-operative CT scan on a day at which the patient is already scheduled to visit our hospital to limit the travel time. Logistical challenges might result in an additional hospital visit.

### **5.1 Investigational treatment**

In this study patients will be randomized between conventional open surgery and open surgery with the assistance of the surgical navigation system. In the conventional approach, imaging findings are processed preoperatively, and translated in actions during surgery by the surgeons brain. With the navigation system the surgeon is provided with a direct real-time correlation between the pre-operative imaging findings and the actual patient anatomy. We hypothesize that the navigation assistance will result in more successful and faster localization of extra-regional lymph nodes. Follow-up imaging will be used to evaluate if all targeted LN are removed. If follow-up imaging with CT or MRI within 3 months after surgery is clinical routine, these data will be used. If imaging is not planned within 3 months, an additional CT scan will be planned by the treating physician.

### **5.2 Use of co-intervention (if applicable)**

No specific restrictions for included patients are specified. Besides the study related procedures, included patients will follow the same pre-operative workup as non-included patients scheduled for a similar operation.

### **5.3 Escape medication (if applicable)**

Not applicable

## **6. INVESTIGATIONAL PRODUCT**

The navigation system used for this study is composed of elements of the Aurora Electromagnetic Measurement System from Northern Digital Inc. (Waterloo, Ontario, Canada) and is combined with in-house developed software for navigation and visualization. The system is developed for use in the NKI-AvL only, and there is no current intent to commercialize the system. According to Dutch national guidelines (beleidsplan medische apparatuur), and agreements between the METC and the department of clinical physics, a tailored safety management and risk assessment protocol is required. All safety management is recorded in the investigational medical device dossier (IMDD) used for all non-CE marked devices. This dossier is composed in close collaboration with the clinical physics department and is added to this application in supplement K1.

### **6.1 Name and description of investigational product(s)**

An extensive description of the investigational product can be found in the IMDD. The navigation system is registered as RT NaviOne system in the NKI-AvL (ID0024519). The used hardware consists of an electromagnetic NDI Aurora V2 tracking system and a standard research PC with monitor mounted on a trolley with a galvanic isolated power supply. The Aurora system consists of an electromagnetic field generator, which is positioned between the table and the patient in a dedicated matras, a system control unit on the trolley, and four sensor interface units which are mounted on the side of the bed. Three Philips Patient Trackers are used to track the position and orientation of the patient during surgery. One sterilized NDI Aurora straight tip probe is used by the surgeon to correlate the actual anatomy with the 3D model.

The used navigation software is in-house developed. An official software release is performed in collaboration with the clinical physics department ([name]) before clinical use. In the release process, the software will be tested on consistency and reliability, and documentation will be stored. The system will be tested in a black-box approach, where an entire chain-test from acquiring CT data until the actual navigation to known positions in a phantom is evaluated. In the navigation software, all available imaging information of the patient can be loaded, including 3D segmentations of the input scans which can be used as a 3D roadmap. In the program, user input is used to semi-automatically localize the Patient Trackers on imaging data. The actual positions of the Patient Trackers are continuously derived from the Aurora system, and the correlation between the 3D roadmap and the actual anatomy is automatically updated. Finally, the tracked probe is digitally projected in the 3D roadmap.

## **6.2 Summary of findings from non-clinical studies**

The navigation system has been extensively tested in a pre-clinical setting (See also IMDD). The electromagnetic tracking accuracy can be influenced by surrounding electronics and ferromagnetic materials. Also, tracking accuracy is known to reduce with increasing distance to the field generator. We have evaluated the tracking accuracy of our navigation setup, and concluded that our OR setup has limited effect [14]. Furthermore, tracking accuracy was within 1 mm root-mean-square error (1SD) in the region between 12 cm (minimum distance) and 35 cm from the field generator. This is the actual region in which we can expect the Patient Trackers and the Probe, and is deemed accurate enough for the application.

## **6.3 Summary of findings from clinical studies**

The navigation system is currently under investigation in a clinical pilot study in which we evaluate its feasibility and safety (N13NAV). The pilot study has been amended to include a maximum of 75 patients as a registration study. An interim analysis was performed after 37 patients. In terms of feasibility, only for one patient the navigation system could not be used during surgery, because the patient was not positioned correctly with respect to the field generator. In terms of safety, none of the procedures resulted in serious adverse events which could be contributed to the use of the navigation system. In all procedures the accuracy/correctness of the system is evaluated on obvious anatomical landmarks (pubic bone, iliac spine, promontory, bifurcations of aorta/iliac arteries) and is corrected if necessary. With the system we are able to localize internal anatomic structures with an accuracy <4 mm. In 4 patients, the navigation system was used for the localization of a locally advanced primary tumour, all resulting in R0 resections. In five out of six patients in which the system was used for localization of a local recurrence an R0 resection was achieved. In one gynaecological recurrence case no R0 was achieved, which was mainly due to a large setup difference between CT and the OR. This procedure was performed before we had intra-operative imaging, which would have been very beneficial. In 25 patients, a total of 71 target lymph nodes were identified on imaging. Sixty-seven out of 71 LNs were actually localized using the tracking system. The four missed LNs consisted of three obturator LNs which were diminished to a size of less than 3 mm after neoadjuvant treatment, and one mesorectal LN which was probably not rigid enough to be localized. Unfortunately, the latter patient developed a local recurrence at the position of the mesorectal LN. In total 15 different surgeons used the navigation system. All surgeons indicated improved anatomical insight, better orientation, and significant additional value of the navigation system. In our experience, use of the system is very intuitive, and novel users directly understand the principle.

#### **6.4 Summary of known and potential risks and benefits**

The main risk of the navigation setup is a miss-registration between the actual patient setup and the 3D anatomical model. If this happens, the surgeon can choose a dissection path through critical pelvic structures such as blood vessels, ureters or nerve tissue. To prevent these errors, obvious anatomical landmarks are used to evaluate the accuracy of the system.

Another potential risk is deformation of the patient anatomy. If this happens, the 3D anatomical model is not representative anymore for the actual anatomy. This risk is minimized by patient selection. The mobility of targets (lymph node, recurrence or primary tumour) is assessed before inclusion by evaluation of the location and position changes between different imaging sessions by imaging experts of the study ([name] & [name]). Only targets which are expected to be rigid with respect to the surrounding bony anatomy or large vessels are included.

The major benefit of the navigation setup is improved anatomical insight during surgery. The navigation system provides a view beyond surgical planes. It provides insight in the optimal surgical approach, and aids in decision making between being radical and preventing morbidity. We have the experience that surgery is performed with more certainty and faster for the so far included cases, which were all deemed surgically challenging.

#### **6.5 Description and justification of route of administration and dosage**

Not applicable

#### **6.6 Dosages, dosage modifications and method of administration**

Not applicable

#### **6.7 Preparation and labelling of Investigational Medicinal Product**

Not applicable

#### **6.8 Drug accountability**

Not applicable

## **7. NON-INVESTIGATIONAL PRODUCT**

There are no non-investigational products used in this study

## **8. METHODS**

### **8.1 Study parameters/endpoints**

#### **8.1.1 Main study parameter/endpoint**

The main study parameter is the percentage of failed procedures, in which failure is defined as: presence of any residual target lymph node on follow-up imaging.

On the pre-operative CT scans, target lymph nodes will be indicated and removal is planned. Cases where the surgeon intraoperatively assess inoperability of a LN due to expected morbidity will be recorded. The actual verification of removal will be done on the first follow-up scan. This should be a CT or MRI scan acquired within 3 months after surgery. The scan will first be registered to the pre-operative CT scan. Two observers ([name] & [name]) will check for each target LN on the planning CT if they are not visible on the follow-up scan. In case of doubt, and for verification of image interpretation, a radiologist will be consulted.

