## SUMMARY

**Rationale:** Lymph node metastasis of pelvic tumours are primarily found along the iliac vessels, the caval vein, aorta, obturator regions, and in the mesorectal and pre-sacral space. Surgical removal of these lymph nodes may be indicated, especially if abnormal on pre-operative imaging. Exact localization of lymph nodes during surgery, however, can be challenging, especially after previous treatment (chemo-radiotherapy and/or previous surgery). We have developed a surgical navigation system which can aid in the localization and removal of lymph nodes. Within the system, the pre-operative imaging information is linked to the actual anatomy during surgery. The navigation system has been evaluated in a pilot study. In 25 patients, 67 of the 71 targeted lymph nodes on pre-operative imaging were actually localized during surgery and removed. These promising results have led to the design of a prospective randomized controlled trial in which the beneficial value of the navigation system for abdominal lymph node dissections will be evaluated.

**Objective:** To assess the beneficial value of our electromagnetic navigation system for targeted lymph node dissection in the abdomen.

**Study design:** Randomized controlled clinical trial.

**Study population:** All patients aged 18 or older, scheduled for open abdominal surgery in which targeted removal of one or more pathological lymph nodes is part of the surgical plan.

**Intervention (if applicable):** After providing informed consent, patients will be randomized between conventional surgery and navigation assisted surgery. In the control arm patients will be operated according to current clinical practice. In the experimental arm, patients will be operated with assistance of a navigation system.

**Main study parameters/endpoints:** Primary endpoint will be the number of failed procedures, in which failure is defined as: presence of any residual target lymph node on follow-up imaging. Secondary endpoints are: time from having the surgical field prepared for lymph node localization to actual removal of the lymph node, overall surgical time, individual LN retrieval rate, blood loss, operator satisfaction, complications, cost, hospital stay, and health related quality of life.

We estimate 40% failed procedures in the conventional arm, vs. 16% in the navigation arm. To achieve sufficient scientific power, we will need 41 patients in each arm.

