### 4.4 Sample size calculation

In the current pilot study (N13NAV), a total of 71 targeted lymph nodes were identified in 25 patients. In total, we failed to localize 4 of the 71 lymph nodes, in four separate patients. We therefore expect to have approximately 16% (4/25) failed procedures in the navigation arm ( $p_B=0.16$ ). In the current pilot study, surgeons indicated in at least 6 patients that certain localized lymph nodes would have not been found without navigation. We therefore estimate a failure rate of 40% ( $p_A=0.40$ ) in the control arm ((6+4)/25). In our study setup we test the following hypotheses  $H_0: p_A = p_B$  and the alternative hypothesis  $H_1: p_A > p_B$  (one-sided alpha). The number of

needed patients per arm with an alpha of 0.05 and a power of 80% is 41. Accrual of all patients is estimated to take 36 months (excluding the time to the first follow-up scan for all).

[figure not shown]

Fig. 2: Screenshot of the 3D anatomical model of a patient during navigation surgery in which the arteries (red), veins (blue), ureters (yellow), bones (white), and pathologic lymph nodes (lime) are shown. The tracked pointer is manipulated by the surgeon in the pelvis of the patient, and is shown in real-time within the 3D model (green). In this example a lymph node was localized in between the internal iliac artery, the internal iliac vein and the ureter

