## 8.2 Randomisation, blinding and treatment allocation

Patients will be randomized according to a randomization scheme provided by the Trial bureau through a website. The randomization scheme is blinded from the surgeons and investigators. In the randomization we will stratify for surgical sub-specialization (surgery, urology, gynaecology), since differences in their approach to the targeted lymph nodes might exist. After receiving informed consent, the researcher will visit the randomization website, provide the specialism, and the patient will automatically be assigned a study number and treatment arm.

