## 10. STATISTICAL ANALYSIS

### 10.1 Primary study parameter(s)

The main study parameter is the percentage of failed procedures, where failure is defined as: presence of any residual target lymph node on follow-up imaging.

The final percentage of failed procedures in both arms will be compared using a one-sided two-proportion z-test. The evaluation will be done on intention to treat, including the lymph nodes which are marked as inoperable during surgery due to expected morbidity.

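### No masking to arm is specified for the readers of the follow-up scan, which is the sole primary endpoint of an open-label surgical trial

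*Protocol*

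**What the plan says.** Section 8.1.1 defines a failed procedure as one with any residual target node on follow-up imaging. Targets are marked on the pre-operative CT. The first CT or MRI within 3 months of surgery is registered to that CT, and two named observers "will check for each target LN on the planning CT if they are not visible on the follow-up scan". The section then adds: "In case of doubt, and for verification of image interpretation, a radiologist will be consulted".

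Nothing in section 8.1.1 says that the observers or the radiologist are masked to arm or that the observers read independently, and it gives no rule for settling a disagreement.

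The one blinding statement is in section 8.2: "The randomization scheme is blinded from the surgeons and investigators". That is concealment of the allocation list. In the same section the researcher enters the patient on the randomisation website, which returns the study number and arm.

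Section 10.1 rests the trial's conclusion on this reading: the failure percentages "will be compared using a one-sided two-proportion z-test".

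**The concern.** Whether a small structure in an operated field is a residual target is partly a matter of judgement. Three of the four nodes missed in the pilot had shrunk below 3 mm (sections 1 and 6.3), and one visible target turns the whole patient into a failure.

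The surgeon must know the arm, and the researcher role in section 8.3 builds the 3D model and sets up the navigation system in the operating room. Masking of the scan reading is therefore the remaining safeguard for the endpoint, and the plan does not specify it. A reader who knows the arm could lean either way on a borderline node, or find doubt in one arm more readily than in the other when deciding which cases reach the radiologist. Such an error cannot be removed in the analysis.

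This is more than a detail left to an analysis plan. The protocol itself fixes who reads, what they compare and when they escalate.

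**Working it through.** **Inputs.** From section 4.4: "approximately 16% (4/25) failed procedures in the navigation arm", 40% in the control arm, one-sided alpha 0.05, power 80%, 41 per arm. From section 10.1: one-sided two-proportion z-test. The protocol gives no reader-error rate, so every error rate below is an assumption.

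**Reproducing the plan's sample size.** With unpooled variance,

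n = (1.645 + 0.842)² × (0.40×0.60 + 0.16×0.84) / 0.24² = 40.19, rounded up to 41.

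This matches the protocol. Exact enumeration of the pooled z-test at 41 per arm gives power of 80.5%.

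**How many readings decide the result.** Expected failures are 0.40×41 = 16.4 and 0.16×41 = 6.6, so about 16 v 7. With a and b failures in the control and navigation arms and p̄ = (a+b)/82,

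z = [(a−b)/41] / √[p̄(1−p̄)×2/41].

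For 16 v 7, p̄ = 23/82 = 0.280 and z = 0.2195/0.0992 = 2.21. Moving navigation patients one at a time from success to failure gives:

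| Control v navigation failures | z | One-sided p |
|---|---|---|
| 16 v 7 | 2.21 | 0.0135 |
| 16 v 8 | 1.94 | 0.026 |
| 16 v 9 | 1.68 | 0.047 |
| 16 v 10 | 1.42 | 0.077 |

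One or two changed readings leave significance intact; the third removes it. Over all significant results possible under the planned rates, 37% would be undone by three or fewer changed navigation readings and 51% by four or fewer.

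**Illustrative effect on type I error.** Assume no true effect, with 28% failure in both arms (the midpoint of 40% and 16%). Let a fraction s of truly failed patients be misread as successes. The observed failure rate in an affected arm is 0.28×(1−s). Exact binomial enumeration at 41 per arm gives:

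| s | Observed rate in affected arm | Type I error, navigation arm only | Type I error, both arms equally |
|---|---|---|---|
| 0 | 28.0% | 5.4% | 5.4% |
| 5% | 26.6% | 7.1% | 5.3% |
| 10% | 25.2% | 9.2% | 5.3% |
| 20% | 22.4% | 15.0% | 5.2% |

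The inflation comes from the difference between arms. Poor reading that is equal in both arms does not produce it.

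**Unit of the error.** Here s applies to failed patients. It equals a per-node miss rate only if each failed patient has one residual node, as in the pilot (four missed nodes in four patients). If half of failed patients had two residual nodes, missed independently (an assumption), a 20% per-node miss rate gives an observed rate of 0.28×(0.5×0.80 + 0.5×0.96) = 24.6% and a type I error of about 10%.

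**The case against.** Four points on the other side deserve weight.

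- **The text is silent; it does not say that readers know the arm.** A reader might infer that the observers are unmasked as a matter of fact, or that they are the same people who build the models and attend surgery. The protocol supports neither. It specifies no masking, and with names removed the observers cannot be matched to the researcher of sections 8.2 and 8.3. What stands is that nothing in the plan prevents an unmasked reading.
- **The radiologist is a safeguard.** One might infer that the radiologist is called only when the observers feel doubt. Section 8.1.1 also provides for verification of image interpretation. The safeguard is still partial: the extent of verification is not stated, the first trigger depends on the observers' own doubt, and the radiologist is not said to be masked.
- **The reading is structured.** Targets are marked in both arms and confirmed with the operating surgeon or urologist (section 8.3), the scans are registered, and two people check each listed node. This narrows the room for judgement but does not close it.
- **The size of any bias is unknown.** The error rates are assumed, and they act in one arm and one direction only. They show sensitivity and do not predict what will happen.

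**Conclusion.** The point holds as a gap in the plan: masking is not specified for either observer or for the radiologist, on the only primary endpoint of a trial whose surgery cannot be masked. The firm figure is the fragility at the planned result, where three changed navigation-arm readings out of 82 patients move p from 0.0135 to 0.077 and two do not lose significance.

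The rise in type I error from 5.4% to 7.1%, 9.2% or 15.0% is an illustration. It depends on a 28% true failure rate in both arms and on patient-level misreading confined to the navigation arm. The documents do not show that such misreading would occur, and it should not be read as the trial's expected false-positive rate.

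The sample size of 41 per arm is not affected.

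**What to change.** In section 8.1.1, state that:

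- the two observers read coded pairs (baseline CT with marked targets, and follow-up scan) in random order, independently, without access to arm, 3D model, intra-operative CT or operating-room record;
- each reading is locked in the electronic case report form before arm is revealed;
- where the existing team allows, an observer does not read patients whose 3D model they built or whose surgery they attended;
- the radiologist already planned sees the same coded images and decides every discordant or doubtful case.

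This is feasible with what is already collected. Both arms have a baseline contrast CT with marked targets and a follow-up scan, and the reading described does not use the intra-operative CT, which only the navigation arm has.

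The cost is the coding work and a locked form field, with no extra scan, reader or patient. The limitation is that masking may be incomplete: in a single-centre trial of 82 patients, an observer who took part in planning or surgery may recognise a case. The change is best made before any follow-up scan is read, because readings already made without masking would have to be repeated.
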